**ClinicalTrials.gov Protocol Registration and Results System (PRS) Receipt**

Release Date: January 1, 2025

**ClinicalTrials.gov ID: NCT06763276**

---

### Study Identification

Unique Protocol ID: İzmirTınaztepeÜ-[name]-001

Brief Title: Preoperative VR Cartoon Viewing Reduces Postoperative Pain and Anxiety in Pediatric Tonsillectomy Patient

Official Title: The Effect of Preoperative Virtual Reality Cartoon Viewing on Postoperative Pain and Anxiety in Children Undergoing Tonsillectomy and Adenoidectomy

Secondary IDs:

### Study Status

Record Verification: January 2025

Overall Status: Completed

Study Start: November 10, 2023 [Actual]

Primary Completion: June 4, 2024 [Actual]

Study Completion: July 13, 2024 [Actual]

### Oversight

U.S. FDA-regulated Drug: No

U.S. FDA-regulated Device: No

U.S. FDA IND/IDE: No

Human Subjects Review: Board Status: Approved

Approval Number: 230-230-14

Board Name: Uşak University Non-Interventional Research Ethics Committee

Board Affiliation: Research ethics commission

[contact]

Email:

Address:

Data Monitoring: No  
FDA Regulated Intervention: No

## Study Description

**Brief Summary:** The aim of this study is to determine the effect of watching a cartoon with a virtual reality headset before surgery on the pain and anxiety levels of children aged 7-12 years.

**Detailed Description:** The aim of this study is to determine the effect of watching a cartoon with a virtual reality headset before surgery on the pain and anxiety levels of children aged 7-12 years. In line with this aim, children aged 7-12 who were scheduled for tonsillectomy and adenoidectomy at the Ear, Nose, and Throat Department of Uşak University Education and Research Hospital were shown a cartoon with a virtual reality headset before surgery, and their pain and anxiety levels were examined. The study was conducted as a randomized controlled experimental study at the Ear, Nose, and Throat Unit of Uşak University Education and Research Hospital. The population of the study consisted of children aged 7-12 who applied for tonsillectomy and adenoidectomy surgery at the Ear, Nose, and Throat Unit of Uşak University Education and Research Hospital. The sample of the study included a total of 102 children, with 51 in the experimental group and 51 in the control group, who met the research criteria and volunteered to participate in the study between November 10, 2023, and June 1, 2024. Data collection tools included the informed consent form, sociodemographic questionnaire, vital signs assessment form, Visual Analog Scale, and the Perioperative Multidimensional Anxiety Scale for children.

## Conditions

**Conditions:** Tonsillectomy  
Adenoidectomy

**Keywords:** Virtual Reality  
Cartoon  
Pain Level  
Anxiety Level

## Study Design

**Study Type:** Interventional  
**Primary Purpose:** Treatment  
**Study Phase:** N/A  
**Interventional Study Model:** Parallel Assignment  
**Number of Arms:** 2  
**Masking:** Single (Participant)  
**Allocation:** Randomized  
**Enrollment:** 102 [Actual]

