| 
Experimental: Virtual Reality Group
 
A meeting was conducted with the children and their parents. Information about the content of the research was provided. Consent forms were completed by the children and their parents. Instructions on how to use the virtual reality headset were given to the children and their parents.
 
Mothers were asked to comfort and caress their children during the preoperative period.
 
The first 15-20 minutes of the cartoon were shown to the children before the surgery. After watching the cartoon, the children were sent for tonsillectomy and adenoidectomy surgery. The remainder of the cartoon was shown one hour after the surgery once the child had settled in the recovery room.
 
Before the tonsillectomy and adenoidectomy surgery, immediately after the child returned to the ward post-surgery, and 8 hours after the surgery:
 
The child's vital signs were recorded. The child's anxiety and pain scores were assessed.
 | 
Virtual Reality Group
 
In the study, a 400-gram virtual reality (VR) headset with an anti-reflective lens system was used, compatible with all earphones with screens ranging from 4.5 to 7.0 inches. The virtual reality (VR) headset, which was lightweight enough for children to wear, was supported on three sides to fit securely on the children's heads and was disinfected after each use. For the experimental group, the compartment at the front of the virtual reality (VR) headset was removed. The earphone was placed into the removed compartment, which was then reinserted. Subsequently, the YouTube virtual reality (VR) feature was activated on the phone, making it ready for viewing.
 |

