| 
No Intervention: Control Group
 
Consent forms were completed by the children and their parents. Mothers were asked to comfort and caress their children.
 
Before the tonsillectomy and adenoidectomy surgery, immediately after the child returned to the ward post-surgery, and 8 hours after the surgery:
 
The child's vital signs were recorded. The child's anxiety and pain scores were assessed. The children in the control group were allowed to watch the cartoon via virtual reality (VR) after all data for the research had been collected to ensure ethical equality.
                                                                                                                                                                                                                                                                                                                                                                                                              |                                                                                                                                                                                                                                                                                                                                                                                                                                                                                                                                                                                                                                                                                                                                    |

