## Eligibility

Minimum Age: 7 Years

Maximum Age: 12 Years

Sex: All

Gender Based: Yes

Accepts Healthy Volunteers: Yes

Criteria: Inclusion Criteria:

Child's criteria:

- Children aged between 7 and 12 years
- Ability to understand pain and anxiety scales
- Possession of communication skills
- Absence of mental issues
- Absence of physical illnesses
- Absence of chronic illnesses
- Willingness of the child and family to participate in the study
- No visual, hearing, or speech problems

Exclusion Criteria:

- Children younger than 7 years or older than 12 years
- Presence of any chronic illness that could affect pain and anxiety levels
- Presence of psychosocial issues
- Children or parents who meet the inclusion criteria but do not wish to wear the virtual reality headset (VRH) glasses
- Children who need to wear glasses other than the virtual reality headset (VRH)
- Children with hearing problems
- Children who do not wish to watch the shrek cartoon

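### The protocol lists the participant as the only masked party, but the headset-versus-nothing comparison it describes left at least the VR-arm children unmasked, so as documented the trial is open label

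*Protocol*

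**What the plan says.** In Study Design, the masking entry of the protocol reads "Single (Participant"). No masking of the caregiver, investigator or outcome assessor is claimed there or elsewhere.

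Arms and Interventions describes the two groups:

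- **VR arm.** "Instructions on how to use the virtual reality headset were given to the children and their parents". "The first 15-20 minutes of the cartoon were shown to the children before the surgery". "The remainder of the cartoon was shown one hour after the surgery once the child had settled in the recovery room".
- **Control arm.** It is labelled "No Intervention: Control Group". Consent forms were completed and mothers were asked to comfort the child, as in the VR arm. Control children were "allowed to watch the cartoon via virtual reality (VR) after all data for the research had been collected".

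The exclusion criteria under Eligibility include "Children or parents who meet the inclusion criteria but do not wish to wear the virtual reality headset (VRH) glasses", and also children unwilling to watch the named cartoon. The inclusion criteria require that the child can understand the pain and anxiety scales.

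Outcome Measures lists blood pressure, heart rate, temperature, haemoglobin, creatinine and glucose as primary. Pain on a 0 to 10 visual analog scale is secondary. Anxiety, on five visual analog items each scored 0 to 100, is under other pre-specified outcomes.

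**The concern.** Masking of the participant is the only protection against knowledge of allocation that the record claims. The intervention is worn on the head and watched, and the comparator is nothing at all until the data are complete. It is hard to see how a child aged 7 to 12 could be unaware of having received it.

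What is at stake is how the pain and anxiety results are read. Both are subjective, and both are what the title and the study aim are about. A child who knows that something was done to help may score lower for that reason alone. A reader who takes the masking entry at face value would assume that this route had been closed at the participant, when the described procedures leave it open.

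**Working it through.** The protocol gives no figure on this point to reproduce, and no arithmetic applies. The check sets the masking entry against the sections that describe what was done.

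1. **What the entry requires.** For participant masking to hold, children in each arm must not know which arm they are in. This usually needs a sham or a comparator that looks alike, or at least a procedure that keeps the contrast from them.

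2. **VR arm.** The child is instructed in the use of the headset, watches 15 to 20 minutes of cartoon before surgery, and sees the rest one hour after surgery. By the assessment on return to the ward the child has already had the first viewing. By the 8-hour assessment the child has had both. The condition in step 1 fails for this arm whatever the controls knew.

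3. **Control arm.** No sham headset, ordinary screen or other attention control is described, and VR is offered only once data collection is over. The information meeting on the content of the research is listed under the VR arm only. However, control children and parents also completed consent forms, and the exclusions for refusing the headset or the cartoon are not limited to one arm. A family can be excluded for refusing the headset only if the headset has been mentioned. This suggests that control families knew of it, but the document does not say when or how the exclusion was applied.

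4. **Any procedure that could supply masking.** None is described in any section. Masking is a property that the protocol itself states, so this is not a detail left to a statistical analysis plan.

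5. **Other parties.** The entry is single masking and names the participant. If that one party was not masked, no masked party remains on the record.

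6. **Which outcomes are exposed.** Pain and anxiety use visual analog scales, and inclusion depends on the child understanding them. Both facts point to rating by the child, although the arm descriptions say only that scores were assessed. Haemoglobin, creatinine, glucose and temperature depend little on what the child knows. The bias therefore falls mainly on the secondary and other pre-specified outcomes.

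**The case against.** The strongest case on the other side has four parts.

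- **Control children may not have known the contrast.** The information meeting appears only under the VR arm, and VR was offered to controls afterwards. This stands as a possibility. A reader might infer that both arms were certainly unmasked and that disappointed controls scored worse. The document makes control-arm knowledge likely but does not establish it, and any disappointment effect depends on that knowledge. The entry is not rescued, because the VR arm is unmasked in any case.

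- **Self-report is not stated.** This is correct. It is a reasonable inference from the type of scale and the inclusion criterion, and should be described as one.

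- **The registered primary outcomes are vital signs and laboratory values.** This is also correct. A reader might infer that every result of the trial is compromised, and the document does not support that. It does not remove the point either, since the brief title claims a reduction in pain and anxiety, and the aim is stated in those terms.

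- **The arm descriptions are plain, so few would be misled, and the trial is complete.** An open-label comparison of this kind is a legitimate design, and correcting the label changes no data, sample size or analysis. This limits the consequence. The stated design property is still wrong.

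**Conclusion.** The point holds. The masking entry is contradicted by the protocol's own description of the arms: at least the VR-arm children knew their allocation, and no other party is stated to be masked. As documented, the trial is open label.

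The consequence is confined mainly to pain and anxiety, and rests on the inference that the child rates both scales. The size of the bias cannot be derived. The protocol gives no standard deviation, target effect, significance level or power, and nothing on expectation effects. A figure built on an assumed bias would only return the assumption.

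A reader might also infer that heart rate and blood pressure, recorded at the same three times, could show whether reporting bias was present. They cannot isolate it. They are already registered primary outcomes, no masked assessor is stated for them, and they respond to surgery, anaesthesia and comforting as well as to anxiety. Neither agreement nor disagreement with the self-rated scores would settle the question.

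**What to change.** Change the masking entry to None (Open Label). If the sponsor can document that another party, such as the person recording the scores, was in fact masked, name that party instead of the participant.

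Wherever conclusions on pain and anxiety are drawn, state that these outcomes were obtained without participant masking. Do not attach a numerical size to the bias, and do not present heart rate and blood pressure as a test for it.

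The cost is one record field and one limitation sentence. The study is recorded as completed, so no data, procedure or analysis changes. The downside is that the stated design looks less rigorous than it does now.

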## Arms and Interventions

| Arms                                                                                                                                                                                                                                                                                                                                                                                                                                                                                                                                                                                                                                                                                                                                                                                                                                                                                                                                                                                                                            | Assigned Interventions                                                                                                                                                                                                                                                                                                                                                                                                                                                                                                                                                                                                                                                                                                             |
|---------------------------------------------------------------------------------------------------------------------------------------------------------------------------------------------------------------------------------------------------------------------------------------------------------------------------------------------------------------------------------------------------------------------------------------------------------------------------------------------------------------------------------------------------------------------------------------------------------------------------------------------------------------------------------------------------------------------------------------------------------------------------------------------------------------------------------------------------------------------------------------------------------------------------------------------------------------------------------------------------------------------------------|------------------------------------------------------------------------------------------------------------------------------------------------------------------------------------------------------------------------------------------------------------------------------------------------------------------------------------------------------------------------------------------------------------------------------------------------------------------------------------------------------------------------------------------------------------------------------------------------------------------------------------------------------------------------------------------------------------------------------------|
| 
Experimental: Virtual Reality Group
 
A meeting was conducted with the children and their parents. Information about the content of the research was provided. Consent forms were completed by the children and their parents. Instructions on how to use the virtual reality headset were given to the children and their parents.
 
Mothers were asked to comfort and caress their children during the preoperative period.
 
The first 15-20 minutes of the cartoon were shown to the children before the surgery. After watching the cartoon, the children were sent for tonsillectomy and adenoidectomy surgery. The remainder of the cartoon was shown one hour after the surgery once the child had settled in the recovery room.
 
Before the tonsillectomy and adenoidectomy surgery, immediately after the child returned to the ward post-surgery, and 8 hours after the surgery:
 
The child's vital signs were recorded. The child's anxiety and pain scores were assessed.
 | 
Virtual Reality Group
 
In the study, a 400-gram virtual reality (VR) headset with an anti-reflective lens system was used, compatible with all earphones with screens ranging from 4.5 to 7.0 inches. The virtual reality (VR) headset, which was lightweight enough for children to wear, was supported on three sides to fit securely on the children's heads and was disinfected after each use. For the experimental group, the compartment at the front of the virtual reality (VR) headset was removed. The earphone was placed into the removed compartment, which was then reinserted. Subsequently, the YouTube virtual reality (VR) feature was activated on the phone, making it ready for viewing.
 |
| 
No Intervention: Control Group
 
Consent forms were completed by the children and their parents. Mothers were asked to comfort and caress their children.
 
Before the tonsillectomy and adenoidectomy surgery, immediately after the child returned to the ward post-surgery, and 8 hours after the surgery:
 
The child's vital signs were recorded. The child's anxiety and pain scores were assessed. The children in the control group were allowed to watch the cartoon via virtual reality (VR) after all data for the research had been collected to ensure ethical equality.
                                                                                                                                                                                                                                                                                                                                                                                                              |                                                                                                                                                                                                                                                                                                                                                                                                                                                                                                                                                                                                                                                                                                                                    |

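### The titles and aim name VR viewing before surgery, but the VR arm also watched after surgery, so the 8-hour and later results belong to the combined package and not to preoperative viewing alone

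*Protocol*

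**What the plan says.** The brief title in Study Identification reads "Preoperative VR Cartoon Viewing Reduces Postoperative Pain and Anxiety in Pediatric Tonsillectomy Patient". The official title is neutral on direction but names the same exposure: "The Effect of Preoperative Virtual Reality Cartoon Viewing on Postoperative Pain and Anxiety in Children Undergoing Tonsillectomy and Adenoidectomy". The aim, given in both the brief summary and the detailed description, is "the effect of watching a cartoon with a virtual reality headset before surgery on the pain and anxiety levels of children aged 7-12 years". None of these mentions viewing after surgery.

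The Arms and Interventions section describes two sessions for the VR arm. The first is before surgery: "The first 15-20 minutes of the cartoon were shown to the children before the surgery". The second is after it: "The remainder of the cartoon was shown one hour after the surgery once the child had settled in the recovery room". Vital signs, pain and anxiety are assessed in both arms at the same three points: "Before the tonsillectomy and adenoidectomy surgery, immediately after the child returned to the ward post-surgery, and 8 hours after the surgery". The control arm could use the headset only once all research data were in.

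Under Outcome Measures, four vital signs, pain and anxiety share those three time points, and the first one after surgery is labelled immediately postoperative. Hemoglobin, creatinine and glucose are measured before surgery and within 24 hours after it.

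**The concern.** The exposure named in the titles and aim is not the exposure that the VR arm received. A reader of the titles, summary and detailed description would not know that children also watched during recovery. If the 8-hour scores are lower in the VR arm, the effect could come from the session before surgery, the session after it, or both together. The brief title credits the first alone. A hospital acting on that title could offer a preoperative session by itself, which this trial did not test at 8 hours.

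**Working it through.** There is no stated figure to reproduce. The check is a timeline, with the end of surgery as 0 h.

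**Inputs**
- Session 1, VR arm: 15-20 minutes, before 0 h (Arms and Interventions).
- Session 2, VR arm: the rest of the cartoon, starting at about 1 h (same section).
- Control arm: no VR before the last data point (same section).
- Assessments: before surgery, on return to the ward, and at 8 h; blood tests within 24 h (Arms and Interventions; Outcome Measures).
- Number of arms: 2 (Study Design).

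**What each postoperative assessment compares**

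| Assessment | Position relative to session 2 | VR arm had received | Control arm had received |
|---|---|---|---|
| Return to ward | Not settled | Session 1, perhaps session 2 | None |
| 8 h | After | Sessions 1 and 2 | None |
| Blood tests within 24 h | After, unless drawn before session 2 | Sessions 1 and 2, with that exception | None |

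**The 8-hour assessment.** Session 2 starts 8 − 1 = 7 hours earlier. Any remainder of the cartoon shorter than 7 hours is finished by then, so the conclusion does not depend on the run time, which the document does not give.

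**The first postoperative assessment.** Two readings are possible. If the recovery room is a stage before the ward, the child returns to the ward after session 2, and the assessment follows it. If the recovery room means the child's room on the ward, an assessment made on arrival precedes a session that starts at one hour, once the child has settled. The label immediately postoperative in Outcome Measures favours the second reading. The document does not state the order.

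**Count of postoperative comparisons**
- 8 h: 4 vital signs + pain + anxiety = 6, all after session 2.
- Laboratory: 3, after session 2 unless drawn earlier.
- Return to ward: 4 + 1 + 1 = 6, order not settled.
- Total: 6 + 3 + 6 = 15. Of these, 6 + 3 = 9 follow session 2 (only 6 if all blood was drawn before it), and 6 are undetermined.

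**Can analysis separate the sessions?** No. As described, both sessions belong to the VR arm and neither to the control arm. No arm received one session without the other, so no model fitted to these two arms can divide an 8-hour difference between them on a randomised basis.

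**The case against.** The strongest reply is that nothing is biased. Allocation was randomised, controls had no VR until the data were complete, and the second session is openly described. The 8-hour contrast is a proper randomised estimate of what the VR arm received, and only its label is too narrow. This stands. A reader might infer that the 8-hour comparison is confounded. For the package it is not; the error lies in attributing the result to one component.

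A second reply is that an assessment labelled immediately postoperative most naturally comes before a session at one hour, so the preoperative claim survives there. This is the more likely reading, and it would be wrong to say that both postoperative assessments are affected. But placing the session in the recovery room and the assessment at return to the ward leaves the order open.

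Two stronger readings go beyond the document. One is that VR children were kept in recovery to finish the cartoon, so that their first assessment came later than in controls. Nothing says that discharge or assessment waited for the cartoon. The other is that most of the exposure was postoperative. That needs a run time that is not given, and a share of minutes viewed is not a share of effect.

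Finally, the trial is completed, pain is a secondary outcome and anxiety is listed under other outcomes. That limits what can be changed but does not remove the point. The brief title's claim concerns pain and anxiety, and the primary vital signs at 8 hours are in the same position.

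**Conclusion.** The titles and aim contradict the intervention described. The 8-hour results, and laboratory results from blood drawn after the second session, estimate the effect of viewing before plus after surgery against no viewing. They cannot support a conclusion about preoperative viewing alone. This covers all six outcomes at 8 hours with certainty and the three laboratory outcomes with the exception stated. For the six outcomes at the first postoperative assessment, a preoperative claim may be sound but cannot be verified from the document.

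The conclusion assumes only that the second session took place as described and that the cartoon's remainder was shorter than 7 hours. It does not show that preoperative viewing has no effect, nor that the later session explains any difference seen at 8 hours. Neither can be judged from this design.

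**What to change.** 1. Reconcile the titles, the aim and the arm description. In the title, aim and conclusion, describe the intervention as perioperative VR viewing, before and after surgery.
2. Attribute the 8-hour results, and laboratory results from samples taken after the second session, only to that package.
3. State whether the first postoperative assessment came before or after the second session, and what the recovery room means in this hospital's sequence.
4. Make a preoperative-only claim at that time point only if, by procedure, the assessment came first for the whole VR arm. Do not select individual VR children whose assessment happened to come first: controls have no second session to match on, and the selection would break the randomised comparison. Do not adjust for the time of assessment either, since it arises after randomisation and may itself be affected by the intervention.

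The cost is a change of wording and a statement of procedure that the study team should be able to supply. No new data are needed. The downside is that the resulting claim is narrower than the current title.
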